### Data management

Data collection forms will be identified by participant number only. Participant contact information and the code linking participant numbers to names will be stored in password-protected files on an encrypted USB key accessible only to AM. These files will be destroyed on completion of study publications. Completed data collection forms will be stored in a locked filing cabinet in a locked office and will be retained for 7 years post-publication as per University of Toronto procedures. Anonymized data will be entered into a spreadsheet stored on a different encrypted USB key before being transferred to statistical software for analysis.

### Statistical analysis

Descriptive statistics will be generated for all variables. Primary and secondary outcome measures will be compared between the pre- and post-intervention groups using t-tests for continuous variables and chi-square statistics for categorical variables. Sub-group analysis will be performed to examine differences in outcomes based on the effect modifiers (program site, parity, food security status and intervention participation) as shown in the conceptual model (Fig. 1). Logistic regression analysis will be used to determine the relationship between breastfeeding self-efficacy scores at 2 months postpartum and breastfeeding practices at 4 and 6 months postpartum, controlling for confounders. All statistical analysis will be performed using IBM SPSS Statistics for Windows, version 26 (IBM Corp., Armonk, N.Y., USA).

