**Methods:**

This pre/post intervention study will examine the effect on breastfeeding outcomes of an evidence-based in-home lactation support intervention provided through the CPNP. We will enrol 210 pregnant women who intend to breastfeed and are registered CPNP clients at two sites in Toronto, Canada. During the intervention phase, postpartum home visits by International Board Certified Lactation Consultants (IBCLCs) will be pro-actively offered to registered clients of the two sites. Double-electric breast pumps will also be provided to those who meet specific criteria. Infant feeding data will be collected prospectively at seven time points from 2 weeks to 6 months postpartum. Descriptive and regression analyses will be conducted to measure intervention effects. The primary outcome is exclusive breastfeeding at 4 months postpartum. Secondary outcomes include the duration of any and exclusive breastfeeding, timing of introduction of breastmilk substitutes and timing of introduction of solid foods. Breastfeeding self-efficacy will be assessed prenatally and at 2 weeks and 2 months postpartum. Other measures include maternal socio-demographics, infant feeding intentions, maternal depression and anxiety, and household food insecurity. Monitoring data will be used to assess the reach, uptake and fidelity of intervention delivery.

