## Methods

### Study design and hypothesis

We will conduct a pre/post intervention study with clients of two CPNP sites in Toronto. Prospectively collected data on infant feeding practices over the first 6 months and breastfeeding self-efficacy scores will be compared between participants who give birth before and after initiation of the lactation support intervention. This quasi-experimental design was chosen as it would not be either ethical or feasible to randomize clients at these community programs targeting vulnerable women to intervention and control groups.

The primary outcome is exclusive breastfeeding at 4 months postpartum. We hypothesize that CPNP clients with access to our lactation support intervention will be more likely to exclusively breastfeed their infants at 4 months postpartum compared with those in the pre-intervention group, and that this effect will be mediated by higher breastfeeding self-efficacy scores. Secondary outcomes are duration of any breastfeeding; duration of exclusive breastfeeding; timing of introduction of breastmilk substitutes (formula); and timing of introduction of solids. We will also assess the rates of any and exclusive breastfeeding and use of expressed breastmilk at each data collection time point up to 6 months postpartum.

Although 6 months is the recommended duration of exclusive breastfeeding, we chose 4 months for the primary outcome analysis as we anticipate that our intervention will improve exclusive breastfeeding primarily by building breastfeeding skills and addressing difficulties in the early postpartum period. Exclusive breastfeeding is frequently compromised after 4 months through early introduction of solids [6, 9], but this practice is less amenable to influence by lactation support provided earlier in the postpartum period.

Monitoring data will be collected and analyzed to determine the reach, uptake and fidelity of the intervention.

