## Discussion

The CPNP is a national initiative which aims to promote and support breastfeeding but currently lacks a formal framework for integrating postpartum lactation support, a key component of enabling women to achieve their breastfeeding goals. This pre/post intervention study aims to examine the effects on breastfeeding practices of pro-actively offering in-home lactation support to vulnerable women through two CPNP sites in Toronto. Feasibility will also be examined through analysis of monitoring data to determine the reach, uptake and fidelity of the intervention. We hypothesize that CPNP clients with access to our lactation support intervention will have higher breastfeeding self-efficacy scores at 2 months postpartum and be more likely to exclusively breastfeed their infants at 4 months postpartum compared with those in the pre-intervention group.

To date there has been limited evaluation of breastfeeding outcomes among CPNP participants. This study will contribute data on infant feeding practices at seven time points in the first 6 months postpartum, and will examine a range of covariates including measures of maternal mental health, household food insecurity and socio-demographic characteristics. Strengths of this research include the prospective data collection, theory-based intervention and inclusion of multiple covariates. AM and the Research Coordinator will attend the weekly program at both CPNP sites, and the Mandarin speaking Research Assistant will attend the weekly GST program. This embeddedness within the programs will contribute to the building of trust and rapport with participants, and is expected to result in high enrollment and retention rates [46]. However, the participant characteristics and infant feeding practices of women registered at the two study sites in Toronto may not be representative of CPNPs across the country and the pre/post study design is not as strong as a randomized trial for determining effectiveness. This research is therefore one step in the process of generating the evidence for appropriate models of integrating lactation support with the CPNP and thereby increasing breastfeeding, health and developmental outcomes for vulnerable infants in Canada.

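### The tests named for the non-randomised pre/post comparison are unadjusted, and the one confounder-adjusted regression does not have study phase as its exposure

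*Protocol article*

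**What the plan says.** All references are to the Protocol article.

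- **Design.** Under Study design and hypothesis, outcomes "will be compared between participants who give birth before and after initiation of the lactation support intervention". The reason given for this design is: "This quasi-experimental design was chosen as it would not be either ethical or feasible to randomize clients". The same section fixes the endpoint: "The primary outcome is exclusive breastfeeding at 4 months postpartum".
- **Test of the phase contrast.** Under Statistical analysis, both primary and secondary outcomes "will be compared between the pre- and post-intervention groups using t-tests for continuous variables and chi-square statistics for categorical variables".
- **Regression.** The same section has one regression: "Logistic regression analysis will be used to determine the relationship between breastfeeding self-efficacy scores at 2 months postpartum and breastfeeding practices". The practices in question are those of months 4 and 6. Confounder control is attached to that sentence.
- **Subgroups.** Outcomes are also to be examined by program site, parity, food security status and intervention participation, all described as effect modifiers.
- **Abstract, Methods.** "Descriptive and regression analyses will be conducted to measure intervention effects".
- **Discussion.** "Strengths of this research include the prospective data collection, theory-based intervention and inclusion of multiple covariates". It also concedes that the design is weaker than a randomised trial.

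**The concern.** The two groups are separated by calendar time, so nothing in the design balances them. The article gives reasons to expect that case mix matters. The Background reports shorter exclusive breastfeeding among women with lower income or education, adolescents, single parents and food-insecure households. The Setting section describes two different sites: newcomers at GST come mainly from China, while HB clients use Spanish, Portuguese and sign-language interpreters and receive extra food support. The Sample size section fixes numbers per phase, not per site within phase. Recruitment conditions also change, because in the intervention phase a coordinator approaches prenatal clients about the service.

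If the phases differ on such factors, a chi-square test attributes the resulting difference in feeding rates to the intervention. The study already collects prenatal predictors that could remove the measured part of this. As the Statistical analysis section is written, they do not enter the phase comparison. What is at stake is the primary effect estimate and its p-value.

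**Working it through.** **1. The plan's own figure.** Inputs from Sample size: 53% before, 73% after, power 0.80, alpha 0.05 (sidedness not stated; two-sided assumed). With pooled variance and no continuity correction:

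n = [1.96·√(2·0.63·0.37) + 0.842·√(0.53·0.47 + 0.73·0.27)]² / 0.20² = 90.3, so 91 per group.

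The article says 93, which gives power 0.81. For attrition, 93/0.90 gives 104; the article says 105. The sample size therefore reproduces, and it rests on an unadjusted two-proportion comparison.

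**2. Where confounder control sits.**

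| Analysis in the Statistical analysis section | Exposure | Adjusted? |
|---|---|---|
| Chi-square and t-tests, primary and secondary outcomes | Phase | No |
| Subgroup analysis | By effect modifier | No pooled adjusted estimate |
| Logistic regression | 2-month self-efficacy score | Yes |

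No row is an adjusted regression on phase, which is what the abstract's sentence would need.

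**3. Illustrative size of the bias.** Assume no true effect, and a binary factor whose prevalence moves between phases.

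- Spurious difference b = (shift in prevalence) × (difference in exclusive breastfeeding between its levels).
- SE = √(2·0.53·0.47/93) = 0.0732, or 7.3 points.
- Rejection probability = 1 − Φ(1.96 − b/SE) + Φ(−1.96 − b/SE).

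Assumed shift of 20 points with a gap of 20 points: b = 0.04 and b/SE = 0.55, giving 0.079 + 0.006 = 8.5%.

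Assumed shift of 20 points with a gap of 30 points: b = 0.06 and b/SE = 0.82, giving 0.127 + 0.003 = 13.0%.

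Letting the SE follow the two rates, the wider range is:

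| Assumed shift | Assumed gap | Spurious difference | Type I error |
|---|---|---|---|
| 0 | any | 0 | 5.0% |
| 10 points | 30 points | 3 points | 6.9% |
| 20 points | 30 points | 6 points | 13.0% |
| 30 points | 40 points | 12 points | 38.3% |

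None of the shifts or gaps comes from the documents.

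**4. Can the data carry an adjusted model?** Expected women not exclusively breastfeeding: 93·0.47 + 93·0.27 = 43.7 + 25.1 = 68.8, about 69. Phase, site, parity, Infant Feeding Intentions score, prenatal self-efficacy score, food security (secure or insecure) and newcomer status make 7 slope parameters, or 69/7 ≈ 9.9 non-events each. Food security in its four categories would add two more.

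**5. Power after adjustment.** Let R² be the squared correlation of phase with the covariates (assumed). Required n = 91/(1 − R²). Any gain from prognostic covariates is ignored.

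| R² | n per group | With 10% attrition | Power at 93 |
|---|---|---|---|
| 0.02 | 93 | 104 | 0.80 |
| 0.05 | 96 | 107 | 0.79 |
| 0.10 | 102 | 114 | 0.77 |
| 0.20 | 114 | 127 | 0.72 |

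**The case against.** The Statistical analysis section is short and does not say that the chi-square test is the sole or final analysis. The abstract does promise regression for intervention effects, and a full protocol or SAP could hold an adjusted phase model. The conceptual model (Fig. 1) is not visible and may list confounders. Comparing phases within site would expose a shift in site mix, and descriptive statistics for all variables would show measured imbalance. The Discussion is open about the limits of the design.

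The documents also give no site-specific feeding rate and no site split by phase. The sites report similar client numbers (222 and 225, over different periods and definitions), and newcomers are a majority at both: 67% at GST, and 106 of 134 new clients (79%) at HB.

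Much of this stands. A reader might infer that the effect will be tested in no other way, or that any case-mix shift will pass as an intervention effect. The documents do not support that, given the abstract's sentence, the subgroup analyses and the descriptive statistics.

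It does not remove the point. The article is not silent on the phase contrast: it names a method, and that method is unadjusted. It places confounder control in a different model, and a list of confounders in the figure would not alter that. Stratified results can reveal a problem but do not supply an adjusted overall estimate.

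**Conclusion.** The concern holds in limited form. The methods stated for the phase comparison are unadjusted in a non-randomised design, and they do not match the abstract. Measured differences between phases would bias the primary estimate.

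The size is unknown. The 8.5% to 13% type I error rests wholly on an assumed spurious difference of 4 to 6 points, and with no shift it stays at 5%. It would be wrong to read these figures as evidence that bias is present, or that the sites differ in exclusive breastfeeding.

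Two further inferences also fail. Adjustment would not make the comparison equivalent to a randomised one: with no concurrent control, secular and seasonal trends remain. Nor is better precision assured, since power may fall if phase correlates with the covariates. The sample size calculation itself is not in error.

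**What to change.** Reconcile the abstract and the Statistical analysis section as follows.

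- **Primary analysis:** logistic regression of exclusive breastfeeding at 4 months on phase, adjusted for a short prespecified set fixed before birth: site, parity, Infant Feeding Intentions score, prenatal self-efficacy score, prenatal food security (secure or insecure) and newcomer status.
- **Reporting:** a standardised risk difference with 95% CI, with the chi-square test kept as a supportive unadjusted result.
- **Excluded from this model:** postnatal self-efficacy (the hypothesised mediator), EPDS and STAI, all measured after the intervention starts.
- **Subgroup analyses:** keep them, described as examining effect modification only.
- **Limitations:** state that secular and seasonal trends remain uncontrolled, and that power may be lost if phase and covariates correlate.

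The cost is analysis wording. Site is known from registration, and Table 1 shows the other covariates are collected prenatally. The planned 105 per group roughly suffices if that correlation is weak (104 needed at R² 0.02, 107 at 0.05). At 0.10 or above, the authors should either accept lower power or recruit more.

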## Background

Breastmilk is a unique food tailored to meet the nutritional, immunological and developmental needs of human infants [1]. The health benefits of breastfeeding are realized in a dose-response relationship to the degree of exclusive breastfeeding, particularly in early infancy [1]. The World Health Organization and Health Canada recommend that all infants be exclusively breastfed (i.e. receive only breastmilk and essential vitamins, minerals and medicines) for the first 6 months of life [2, 3]. However, achievement of this goal remains elusive. Globally, only 42% of infants under 6 months of age are exclusively breastfed [4]. National data show that 90% of Canadian mothers initiate breastfeeding, but nearly half discontinue within the first 6 months and only 32% exclusively breastfeed for 6 months [5]. Exclusive breastfeeding is compromised by a variety of practices, particularly formula supplementation and early introduction of solids [6, 7]. Exclusive breastfeeding duration is lower among vulnerable women in Canada, such as those with lower income and education levels, adolescents, single parents and those living in food insecure households [8–12]. Global systematic review evidence indicates that immigrant women are more likely to initiate and continue breastfeeding than their native-born counterparts, likely reflecting social norms regarding breastfeeding in many countries of origin, but exclusive breastfeeding is a universal challenge [13].

Two key contributors to both early cessation and non-exclusive breastfeeding are the perception of insufficient breastmilk supply and unresolved breastfeeding difficulties [14–17]. Access to skilled lactation support in the early postpartum period can be vital to addressing these concerns and supporting women to achieve their breastfeeding goals [18]. Underlying these concerns is breastfeeding self-efficacy, a construct drawn from Bandura’s social-cognitive theory and defined as a woman’s confidence in her ability to breastfeed her new baby [19]. Women with high breastfeeding self-efficacy are better able to overcome common challenges and continue breastfeeding [19]. Theory-based postpartum lactation support interventions have been shown to improve breastfeeding self-efficacy, duration and exclusivity [20, 21].

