### Data collection

Data will be collected in person or by telephone either by AM or by a Mandarin speaking Research Assistant. Professional interpreter services will be used as required for other non-English speaking participants.

All primary and secondary outcome measures will be assessed through prospective data collection using a standardized and validated Infant Feeding Questionnaire developed by [name]’s research group and used in several prior research studies at the Hospital for Sick Children in Toronto [35]. This questionnaire will be administered to study participants at 2 weeks postpartum, and then monthly until 6 months for a total of seven infant feeding data collection points (Table 1). At each time point, participants will be asked to report the average number of daily milk feeds their infant received in the past 2 weeks, divided into feeds at the breast, expressed breastmilk feeds, and formula feeds. Provision of cow’s milk, non-milk fluids and vitamin or mineral supplements will also be recorded. Participants who stop breastfeeding will be asked for the last date breastmilk was provided and the main reasons for cessation. If applicable, the date of solids introduction and the name of the first food will be recorded.

**Table 1 Tab1:** Data collection timeline

Study Instrument	Prenatal	Postnatal Data Collection						
		2 weeks	1 month	2 months	3 months	4 months	5 months	6 months
Maternal Socio-demographics Questionnaire	√							
Infant Feeding Intentions Scale	√							
Prenatal Breastfeeding Self-Efficacy Scale	√							
Household Food Security Questionnaire	√							√
Breastfeeding Self-Efficacy Scale-Short Form		√		√				
Infant Feeding Questionnaire		√	√	√	√	√	√	√
Edinburgh Postnatal Depression Scale				√				
State-Trait Anxiety Inventory for Adults				√				
Six Months Postpartum Questionnaire								√

We hypothesize that the intervention effects will be mediated through increases in breastfeeding self-efficacy, which will be assessed at 2 weeks and 2 months postpartum using the Breastfeeding Self-Efficacy Scale-Short Form [36]. Additional data collection tools are listed below. The Socio-demographics and 6 Months Postpartum questionnaires were developed for this study, with income-related questions drawn from Statistics Canada’s Employment Insurance Coverage Survey [37]. The remaining instruments are validated scales from the literature, all of which have been used previously with vulnerable populations.

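### The four secondary outcomes are times to an event cut off at 6 months, but the analysis section gives them only a t-test, which does not handle women without the event

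*Protocol article*

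**What the plan says.** Under Study design and hypothesis, the protocol article names its secondary outcomes: "Secondary outcomes are duration of any breastfeeding; duration of exclusive breastfeeding; timing of introduction of breastmilk substitutes (formula); and timing of introduction of solids". Each is a time from birth to an event.

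Under Data collection, the feeding questionnaire is "administered to study participants at 2 weeks postpartum, and then monthly until 6 months for a total of seven infant feeding data collection points", so observation ends at 6 months. Two of the events have a described date, and each date is taken only once the event has happened: "Participants who stop breastfeeding will be asked for the last date breastmilk was provided" and "If applicable, the date of solids introduction and the name of the first food will be recorded".

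Under Statistical analysis, the group comparison is one sentence. It covers the primary and the secondary outcomes alike, which are to be "compared between the pre- and post-intervention groups using t-tests for continuous variables"; categorical ones go to a chi-square test instead. The only regression described there has another purpose: "Logistic regression analysis will be used to determine the relationship between breastfeeding self-efficacy scores at 2 months postpartum and breastfeeding practices at 4 and 6" (the last two being ages in months). It does not compare durations between the two groups. No Kaplan-Meier, log-rank, Cox or restricted-mean analysis is mentioned.

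The Background section says of Canadian mothers that "nearly half discontinue within the first 6 months and only 32% exclusively breastfeed for 6 months".

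**The concern.** A duration that has not ended by 6 months, or by the last contact before dropout, is right-censored: it is known only to exceed that time. A t-test needs one number per woman. The analyst must therefore either leave out women without an event or enter the censoring time as if it were an event time. The plan does not say which.

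The first choice compares only women who stopped early and removes the successes. An intervention that works by moving women past 6 months would then leave little trace in the comparison. The second choice is far milder, but it treats dropouts as if they had stopped and loses power. All four listed secondary outcomes are of this kind, so how the study's duration results read depends on an unstated data-handling decision.

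**Working it through.** **The plan's own figure.** The Sample size section gives 93 per group for 53% against 73%, alpha 0.05, power 0.80. With two-sided alpha assumed, pooled variance and p̄ = 0.63:

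n = [1.96·√(2·0.63·0.37) + 0.8416·√(0.53·0.47 + 0.73·0.27)]² / 0.20² = (1.338 + 0.562)² / 0.04 ≈ 90.3, so 91.

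This is close to 93, where power is 0.81. Recruiting 105 leaves 105 × 0.9 = 94.5 after 10% attrition. The figure concerns the binary primary outcome and is not in dispute.

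**Which test falls on which outcome.** The section does not list its continuous variables. The primary outcome is binary, so among the named primary and secondary outcomes the t-test can apply only to the four durations and timings. The one alternative offered, chi-square, does not handle censoring either.

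**How many women have no event by 6 months.**
- Any breastfeeding: nationally more than half continue, so more than about 46 of every 93.
- Exclusive breastfeeding: nationally 32%, or 0.32 × 93 ≈ 30 of 93.
- Exclusive breastfeeding, projected from the program's 4-month rates with a constant hazard: 0.53^(6/4) = 0.386 before the intervention and 0.73^(6/4) = 0.624 after.
- Formula and solids: no share is given. A woman still exclusive at 6 months has introduced neither, so 32% is a national lower bound for both.

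**What each use of the t-test estimates** (exclusive breastfeeding, program rates, no attrition). The hazards are λ = −ln(0.53)/4 = 0.1587 and −ln(0.73)/4 = 0.0787 per month, a ratio of 0.496.
- Mean time restricted to 6 months, (1 − S₆)/λ: 0.614/0.1587 = 3.87 and 0.376/0.0787 = 4.78. Difference 0.91 months.
- Mean among women with an event, 1/λ − 6·S₆/(1 − S₆): 6.30 − 3.77 = 2.53 and 12.71 − 9.95 = 2.76. Difference 0.23 months, about a quarter of the restricted-mean difference.

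**Power.** Simulation with 105 per group, exponential durations, hazard ratio 0.5, a cut-off at 6 months, and 10% lost uniformly between 0.5 and 6 months. Repeat runs differ by about one percentage point.

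| Scenario (pre-intervention group) | t-test, recorded dates only | t-test, 6 months or last contact entered | Log-rank | Mean difference with last contact entered vs true restricted-mean difference (months) |
|---|---|---|---|---|
| Any breastfeeding, 52% continuing at 6 months | 7% | 70% | 85–86% | 0.67 vs 0.71 |
| Exclusive, 32% at 6 months | 14% | 90% | 96% | 0.94 vs 0.99 |
| Exclusive, 53% at 4 months | 10% | 85% | 93–94% | 0.86 vs 0.91 |

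The shortfall in the last column is about 5–7% toward the null. With a hazard ratio of 1, all three tests reject in about 5% of trials. Without attrition, the any-breastfeeding row becomes 77% for the t-test with 6 months entered and 86% for log-rank.

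**The case against.** The strongest reply is that the protocol nowhere says women without an event will be dropped. Feeding data are collected on every woman at seven points, so entering 6 months for those still breastfeeding is just as plausible. With complete follow-up, that t-test is a valid comparison of means restricted to 6 months, one of the remedies proposed here. This stands. A reader might infer that the planned analysis will nearly erase a true effect; the documents do not support that, because the very low power belongs to only one of two possible implementations. Nor do they support a claim of false positives, since type I error stays near 5% either way.

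Other points also stand. The 6-month shares are national background figures, not program data. The hazard ratio of 0.5 follows from 53% to 73% for exclusive breastfeeding but is only an assumption for any breastfeeding. Formula and solids were not simulated, and a constant hazard from birth would be implausible for solids, which the article describes as often introduced early, after 4 months. Rates of any and exclusive breastfeeding are also to be assessed at each time point, which gives a censoring-free view of two of the four outcomes among women still in contact.

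It can also be said that the article is condensed: the abstract promises regression analyses of intervention effects, and the durations are never assigned to a t-test by name. This helps less. The analysis section does state a rule for secondary outcomes, and neither test in that rule suits a censored time. The point is a method that is stated and does not fit, not a detail left to a fuller document.

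**Conclusion.** The concern holds for the secondary outcomes and should be fixed. The stated tests do not fit four right-censored outcomes, and the size of the harm depends on handling that the article leaves open. With recorded dates only, power is about 7–14% and most of the effect is hidden. With 6 months or last contact entered, the cost is a bias of about 5–7% toward the null under 10% attrition, and power of about 70% against 85–86% (any breastfeeding) or 85–90% against 93–96% (exclusive). These sizes rest on exponential durations, a hazard ratio of 0.5, 105 recruited per group, uniform dropout, and national or projected 6-month shares. For formula and solids the argument is structural and no size is claimed.

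A reader might take this as undermining the trial's main result. It does not: the primary outcome is binary at 4 months, and its test and sample size are untouched.

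**What to change.** In the Statistical analysis section, take the four durations and timings out of the t-test sentence. Compare them with Kaplan-Meier curves and log-rank tests. Estimate the effect either by Cox regression with prenatal covariates named in advance, or by the difference in restricted mean time to 6 months. Censor women without the event at last contact or at 6 months. The covariates have to be listed, because the section describes no adjusted model for the group comparison that could be borrowed. Keep t-tests for questionnaire scores such as breastfeeding self-efficacy.

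The cost is a change of analysis wording and some analyst time. Survival methods are available in the SPSS package the article names. No visits, outcomes or participants are added.
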